Besides its quantitatively measurable long-term health benefits, 16:8h-IF has recently been shown to improve quality of life (QoL) and especially the domain of fatigue in a generally healthy study population (9). These results are of great importance not only for mainly healthy people suffering from psychological or physical stress for instance due to shift work, but also for patients with cancer undergoing anti-neoplastic therapies. Especially chemotherapy (CHT) is often associated with a drastic reduction in QoL and increased fatigue, with around 62% of patients suffering from fatigue during treatment (10) and about one third still suffering from it half a year later (11). While some side effects of CHT can be sufficiently treated with modern drugs (e.g. antiemetics, analgesics), there is still a tremendous lack of treatment options for chemotherapy-induced side effects including fatigue (12). Recently, STF has shown to increase QoL and tolerance to CHT in 34 patients with ovarian and breast cancer (13) and the results of a randomized-clinical multi-center trial on STF during CHT are eagerly awaited (8). In contrast, in the DIRECT trial, de Groot et al. found no effect for a fasting-mimicking diet on QoL during CHT in 131 women with breast cancer compared to a regular diet. However, it has to be noted that solely 20% of patients in the fasting-mimicking diet group completed the trial according to the protocol guidelines. The authors report a dislike of distinct components of the fasting-mimicking diet, perhaps induced by the CHT as the main reason for non-compliance and premature discontinuations in the intervention group (14).

IF could be a promising alternative to fasting-mimicking diets, due to its non-calory restrictive and non-ingredient restrictive eating period, which offers freedom in food choice to all patients. The everyday compatibility of IF has demonstrated a high compliance of 90% in a trial conducted by our group (9).

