#### Chemotherapy-related toxicities

To assess the effect of IF on chemotherapy-related toxicities (hematological and non-hematological toxicities), the incidence and severity of treatment-related adverse events (AEs) will be recorded by the Common Terminology Criteria for Adverse Events (CTCAE, v5.0). Laboratory measures focused on hematological toxicities, renal and liver functions as well as specific biomarkers for metabolism and tumor immunology (see **Table 1**) will be analyzed during the whole study period.

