### Statistical analysis

Patients will be randomized to the intervention or control group (1:1) stratified by tumor entity and study site. The primary endpoint, the difference of the mean change of fatigue over a period of three months as measured by the FACIT-FS© score, will be compared between both groups using mixed models. Confounders such as age, type of CHT, neoadjuvant/adjuvant vs metastatic treatment, the Eastern Cooperative Oncology Group performance status (ECOG), histological tumor grade, and Fédération Internationale de gynécologie et d’Obstetrique (FIGO) -stage will be included in the mixed models. Laboratory data, as well as QoL questionnaire-based outcomes will also be assessed using mixed models. Missing data for the primary outcome as well as secondary outcomes with the potential to become main outcomes in subsequent larger trials will be imputed. Where possible, missing questions from FACT^©^ questionnaires will be prorated using the average of the other answers in the subscale (prorated subscale score = [sum of the item scores]*[N of items in subscale]/[N of items answered]) as long as more than 50% of the items are answered. Data will be imputed by drawing values from the distribution of the control group (jump to reference).

A comprehensive summary will be given for primary and secondary endpoints, including absolute and relative frequencies for categorical and binary variables as well as mean and standard deviation or median and interquartile range and minimum-maximum for all data with at least interval scale level. Pathological response rates after neoadjuvant CHT will be compared using the Chi square test. Radiological response rates (complete response, partial response, stable disease, and progressive disease) will be compared between the arms at 3 months and 6 months using the Mann-Whitney-U-tests. The occurrence of any adverse event as well as the occurrence of grade 3 or higher adverse events will be compared between both groups using the Chi square test. And a list of immunological and metabolic parameters will be compared between both groups using the Mann-Whitney-U test. A paired Wilcoxon test will be used to compare the change in BMI over three months between both groups.

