Analyses will be performed as (1) modified intention-to-treat (ITT) population including all patients randomized who have at least received the first chemotherapy cycle. Patients will be analyzed in the group they were randomized to; (2) per-protocol (PP) sets, including all patients who have at least completed one/two/three or all chemotherapy cycles without major protocol violations. Safety will only be assessed in the per-protocol subset. Subgroup analyses will be performed by tumor type and type of CHT regime for groups with an adequately high number of participants. Furthermore, the parameters will be displayed graphically, and appropriate descriptive statistics will be employed. The significance level will be bilaterally set at 5%. 95% confidence intervals will be reported where appropriate. Due to the exploratory nature of secondary outcomes, no adjustments will be made for multiple testing.

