### Sample size

Sample size calculations were based on a recently published study by Bauersfeld et al. assessing short-term fasting during chemotherapy of breast and ovarian cancer patients (13). A sample size of 48 patients per group is necessary to detect a mean difference of 9.1 points on the FACIT-FS^©^ scale with a standard deviation of 13.7 points and a power of 90% and α=0.05 with a two-sided independent t-test. To account for possible drop-outs, a sample size of 55 per group at baseline is planned.

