### Limitations

With increased generalizability due to the inclusion of different cancer types and CHTs (+/- immunotherapy), comes a greater heterogeneity in trial results. Thus, the secondary endpoints of this clinical trial are only exploratory. However, these exploratory results are essential for generating new hypotheses, detecting meaningful endpoints and better sample size estimations for future clinical trials. Depending on the distribution of included patients, the data might be of limited significance for some cancer types or CHT regimes. Especially, the type of cancer therapy greatly influences the magnitude of the experienced QoL impairment. Thus, in this trial only i.v. CHTs including at least one alkylating agent or topoisomerase inhibitor are allowed. Furthermore, we assess the difference in mean change with regards to CHT regimes to minimize the effects of different CHT regiments on the results. In addition, many side effects of CHT such as fatigue, limited concentration abilities, physical weakness or gastrointestinal symptoms are common in most i.v. CHTs. Thus, the results of this trials should be generalizable especially with regards to QoL independent of the distribution of patients. A confounding factor of our study could be that the fasting period parallels over the cause of the year with the hay fever and summer season, which in itself may lead to increased fatigue in some subjects, diminishing possible effects (26). However, by comparing long-term effects we aim to limit intermittent periods of increased fatigue and expect the fatigue induced by CHT to exceed allergy related symptoms.

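### One of the two planned adverse-event tests, the chi-square on occurrence of any adverse event, is likely to have little power in either direction, and neither test uses the ordered CTCAE grade that is collected

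*Protocol article*

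**What the plan says.** Tolerance of chemotherapy is in the article's title. Under Chemotherapy-related toxicities, "the incidence and severity of treatment-related adverse events (AEs) will be recorded by the Common Terminology Criteria for Adverse Events (CTCAE, v5.0" is the stated means of assessing the effect of fasting on haematological and non-haematological toxicity. The Statistical analysis section then fixes the tests: "The occurrence of any adverse event as well as the occurrence of grade 3 or higher adverse events will be compared between both groups", by chi-square. Both variables are yes/no per patient. The sentence directly before it compares ordered radiological response categories by Mann-Whitney test.

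On the level, "The significance level will be bilaterally set at 5" per cent. Secondary outcomes are exploratory and unadjusted for multiplicity, and 95% confidence intervals are promised where appropriate. Other safety information is planned: BMI change, blood counts, and liver and kidney values, with laboratory data analysed by mixed models.

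No any-event rate or grade 3 or higher rate is given. The Introduction describes chemotherapy as associated with loss of quality of life and fatigue, "with around 62% of patients suffering from fatigue during treatment". The Limitations section adds that "many side effects of CHT such as fatigue, limited concentration abilities, physical weakness or gastrointestinal symptoms are common in most i.v. CHTs".

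**The concern.** A yes/no variable that is already positive in most control patients has little room to rise. Fatigue alone is put at about 62%. Adding gastrointestinal symptoms, weakness and blood-count toxicity over 12 weeks makes a much higher any-event rate plausible. The any-event test would then usually be non-significant whether or not fasting changes tolerance by a relevant amount.

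The second test, grade 3 or higher, does not have this ceiling at moderate rates. However, it cannot see a move from grade 1 to 2 or from 3 to 4, and neither can the any-event test. The severity grades are collected, but no planned adverse-event test uses their order. At stake is how much the trial can say, even exploratively, on one of its title questions.

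**Working it through.** **The plan's own figure.** The sample size was set for FACIT-FS only: "to detect a mean difference of 9.1 points on the FACIT-FS^©^ scale with a standard deviation of 13.7 points", with "a power of 90% and α=0.05 with a two-sided independent t-test". Normal approximation: n = 2 × (1.960 + 1.282)² × 13.7² / 9.1² = 2 × 10.51 × 2.2665 = 47.6, so 48 per group. The stated figure is reproduced (an exact t calculation gives 48.6, and 89.6% power at 48). The planned 55 allows for 1 − 48/55 = 12.7% drop-out. No power is stated for the adverse-event tests. Both 48 and 55 per arm are used below, because drop-outs are expected and safety is restricted to the per-protocol subset.

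**Assumptions, not in the documents.** Control any-event rate 85 to 98%; control grade 3 or higher rate 30 to 50%; true effect a 0.5 SD shift in a latent normal worst-grade severity. The fasting-arm rate is p_IF = Φ(Φ⁻¹(p_C) ± 0.5). Power is by exact binomial enumeration of the uncorrected Pearson chi-square, critical value 3.84.

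**Any-event test, 55 per arm.**

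| Control rate | Fasting rate, harm | Power, harm | Fasting rate, benefit | Power, benefit |
|---|---|---|---|---|
| 85% | 93.8% | 32% | 70.4% | 46% |
| 90% | 96.3% | 24% | 78.3% | 39% |
| 95% | 98.4% | 13% | 87.4% | 29% |
| 98% | 99.5% | 2% | 94.0% | 16% |

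At 48 per arm, power runs from 31% to 1% towards harm and from 41% to 15% towards benefit.

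**The ceiling.** Suppose every fasting patient has an event and k of N controls have none. Then chi-square = 2Nk / (2N − k). For N = 55, k = 3 gives 330/107 = 3.08 and k = 4 gives 440/106 = 4.15. For N = 48, the values are 288/93 = 3.10 and 384/92 = 4.17. At least four event-free controls are therefore needed. At a 98% control rate and N = 55 only 55 × 0.02 = 1.1 are expected, and the chance of four or more is 2.4% (1.5% at N = 48).

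**Grade 3 or higher, same harmful shift.** Control rates of 30, 40 and 50% become 49.0, 59.7 and 69.1%. Power is 53 to 54% at 55 per arm and 48 to 50% at 48 per arm.

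**Ordinal comparison.** A Mann-Whitney test on worst grade in five ordered levels, simulated under the same shift, has about 62% power at 48 per arm and 69% at 55, with type I error of about 5%. The exact figure moves by a few points with the assumed spread of grades.

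**As pairs.** The fair comparison is of both tests together. Under the harmful shift, at least one of the two planned chi-square tests rejects in about 49 to 66%. Worst-grade Mann-Whitney plus the retained grade 3 or higher test rejects in about 65 to 72%. Joint type I error is similar or lower for the second pair at any-event rates of 85 to 95%. At 98% that is not so, because there the any-event test hardly ever rejects.

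**The case against.** A reader might infer that toxicity and safety rest on the any-event test, so that a null result says nothing about tolerance. The documents do not support that. The same sentence names grade 3 or higher, and BMI, laboratory mixed models and discontinuations are also assessed.

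A reader might also take a rate near 100% as given. It is an assumption, and it matters: at a 90% control rate against 100% in the fasting arm, power is 72% (48 per arm) or 81% (55 per arm). That case requires every fasting patient to have an event, however. Under the 0.5 SD shift, power at 90% is about 24 to 25%, and even at a 62% control rate it is only 50% with 55 per arm.

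The ceiling limits increases rather than reductions, and the trial expects a reduction. For 98% against 85%, power is 72 to 74%. That is a large effect; for the 0.5 SD shift towards benefit, power is still only 46% down to 16%.

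Toxicity is exploratory, intervals are promised where appropriate, and tabulation by grade may be in the full protocol or analysis plan. Nothing says that a null result will be read as safety; that is a foreseeable risk, not a stated plan. These points lower the weight of the concern but leave the choice of test as it stands, since the article fixes it explicitly.

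A uniform latent shift favours an ordinal test. If harm were purely a 20-point move from grade 2 to grade 3, worst-grade Mann-Whitney would have only 14 to 20% power, against 55 to 59% for grade 3 or higher. This stands, and it is why the grade 3 or higher test must be kept.

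**Conclusion.** The point holds for one of the two planned adverse-event tests. At assumed control rates of 85 to 98% and a 0.5 SD shift, the any-event chi-square has about 32% to 2% power towards harm and 46% to 16% towards benefit at 55 per arm. The grade 3 or higher test reaches about 48 to 54% for the harmful shift. Replacing the any-event test by an ordinal one raises the pair from about 49 to 66% to about 65 to 72%. The gain is small at an 85% rate and largest at 98%.

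This does not empty the safety assessment, and it does not touch the primary endpoint. It rests on event rates and a severity model that the documents do not supply. It is an improvement worth making because it is cheap and uses a test the same section already applies to another ordered outcome.

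**What to change.** In the Statistical analysis section:

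- Replace the any-event chi-square with an ordinal comparison of each patient's worst CTCAE grade over the active period, by Mann-Whitney test or proportional-odds model, reported with a 95% confidence interval.
- Keep the grade 3 or higher comparison and report it as a risk difference with a 95% confidence interval.
- Show any-event frequencies descriptively.
- State that the confidence limits are what is reported, and that a non-significant result is not evidence of equal tolerance.

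The cost is a reworded passage of a few lines. The grades are already collected, so no patients, visits or data are added. A rank effect or odds ratio is less readable than a percentage, which the descriptive table offsets. Worst grade still pools all toxicities and can be less sensitive to an isolated move from grade 2 to 3, so it should not displace the grade 3 or higher comparison.

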Questionnaires *Fatigue → FACIT-FS©General QoL → FACT-G© General wellbeing → EORTC QLQ-C30© TOI mental health TOI physical healthTumor specific FACT-B© FACT-O© FACT-Cx© FACT-En©Pelvic floor functionalitySleeping qualityAdherence diary Continuation/Acceptance/ Difficulties		XXXXXXXXXX^4^X^5^X^6^	XXXXXXXXX	XXXXXXXXX	XXXXXXXXXXXX →		XXXXXXXXXXX

* Some questionnaires can be calculated as subgroups from other questionnaires. Thus, only 2-3 questionnaires will need to be completed by the participants.

^1^ y-H2AX DNA damage essay will only be performed on the day of chemotherapy at cycle 1 day 1, after 6 weeks and after 12 weeks.

^2^ The immunological response will only be assessed at baseline (day of enrollment), as well as one week after chemotherapy is given at three time points (week 1, week 7 and week 13).

^3^ Radiological response will only be assessed in patients treated neoadjuvantly for ovarian/peritoneal or cancer of the fallopian tubes (response rate to neoadjuvant CHT), as well as in metastasized patients of all included tumor types.

^4^ Pelvic floor functionality will only be checked on day 1 of cycle 1; 12 weeks after the start of chemotherapy and during the 6 month follow-up.

^5^ Sleeping quality will only be checked on day 1 of cycle 1; 12 weeks after the start of chemotherapy and during the 6 month follow-up.

^6^ Adherence will only be checked via a daily diary in the intermittent fasting group.

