#### Immunological response

In a recent study cyclic fasting during chemotherapy showed to downregulate peripheral blood immunosuppressive myeloid cells while increasing activated/cytotoxic cells (21). Thus, we plan to perform a multicolor flow cytometry 7 days after the administration of chemotherapy during the active trial period at 1 week, 7 weeks and 13 weeks. As the immunological changes are dependent on the day CHT is given, time points will be adjusted +/- 1 week depending on the days CHT is administered (e.g. in case of delayed CHT or public holidays). The blood samples will be stored in X-VIVO-medium with 10% DMSO (1 x 10^7^ cells/mL) at -80°C. Peripheral blood mononuclear cells (PBMCs) will be isolated from venous whole blood of the patients by gradient centrifugation. 10 ml blood will be separated by Ficoll using Leukosep tubes (Greiner) after lysis of erythrocytes (RBC lysis solution, Qiagen). The detection of leukocyte surface markers will be performed by using fluorochrome conjugated antibodies specific for CD3, CD8, CD14, CD15, CD25, CD56, CD69, HLA-DR, PD-L1 and PD1. Monocytes will be indicated by CD14 expression, PMN-MDSCs by CD15 expression, M-MDSCs by CD14 expression but HLA-DR negativity, PD-L1 positive immunosuppressive monocytes by CD14 and PD-L1 expression, T cells by CD3 expression and cytolytic NK cells by CD16 and CD56^dim^ expression of CD3 negative cells (21). To detect further immunological reactions, the cytokines CCL2, G-CSF, IL-6 and IL-8 will be quantified by ELISA (R&D Systems).

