To ensure the safety and exclude negative effects on the anti-tumor activity of CHT through the periodic activation of the ketogenic metabolism for energy production by IF, several laboratory values reflecting the general health in blood samples will be drawn regularly. Several studies suggest significant changes in laboratory parameters including a decrease in blood glucose levels and HbA1C (30, 37), serum cholesterol, liver profiles (46) and oxidative stress (2, 3). Furthermore, growth factors such as IGF-1 have been associated with decreased side effects during systemic chemotherapy (47, 48). Thus, we aim to explore the changes in meaningful disease-associated blood values caused by IF, such as IGF-1, interleukin 6 and 8 as well as tumor markers. Finally, regular basic values including liver and kidney function are checked to ensure the safety of IF during CHT.

Recently, Vernieri et al. demonstrated a change in peripheral blood mononuclear cells caused by a fasting mimicking diet during chemotherapy in breast cancer patients. They were able to show a downregulation of immunosuppressive myeloid cells while simultaneously activating cytotoxic cells (21). Unfortunately, only 20% of patients were able to comply with the fasting schedule for a total of eight cycles. Similar results in compliance were seen in a trial by de Groot et al. using a fasting mimicking diet during CHT in patients with breast cancer (14). Interestingly, they were able to show a reduction in peripheral cell damage (measured by the level of y-H2AX) in those compliant with the diet, indicating a protection of healthy cells without limiting the cytotoxic effects on cancer cells. So far, no evidence exists assessing the influence on immunological changes and peripheral cell damage during CHT in patients with gynecological cancers. Thus, we aim to assess these changes in our cohort.

In summary, the IFAST trial is of great importance to evaluate the effect of IF on fatigue during CHT to offer patients an alternative of actively influencing their well-being during cancer treatment. Furthermore, this trial will help to gain more insight on the effects of fasting on the immune system and efficiency and tolerance of chemotherapy, despite being exploratory.

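### Immunological and metabolic markers fall under both mixed models and a Mann-Whitney test, with no statement of which result stands or what is ranked

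*Protocol article*

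**What the plan says.** All of this is in the protocol article.

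- **Statistical analysis, first rule:** "Laboratory data, as well as QoL questionnaire-based outcomes will also be assessed using mixed models". Just before this, the section lists the covariates for its mixed models, among them age, type of chemotherapy and ECOG status.
- **Statistical analysis, second rule,** one paragraph later: "a list of immunological and metabolic parameters will be compared between both groups using the Mann-Whitney-U test". It gives no variable (raw value or change), no time point and no order of precedence.
- **Statistical analysis, next sentence, for contrast:** "A paired Wilcoxon test will be used to compare the change in BMI over three months between both groups". Here the change is named.
- **Chemotherapy-related toxicities:** the sentence on laboratory measures covers haematological, renal and liver values and also "specific biomarkers for metabolism and tumor immunology".
- **Discussion:** glucose and cholesterol are called laboratory parameters, and the stated aim is "we aim to explore the changes in meaningful disease-associated blood values caused by IF".
- **Table 1, footnote 2, and Immunological response:** there is a sample at enrolment, then samples "at 1 week, 7 weeks and 13 weeks".
- **Statistical analysis, end:** tests are two-sided at 5%. Secondary outcomes are exploratory and not adjusted for multiplicity.

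**The concern.** One class of markers is covered by two analysis rules in the same section. A mixed model and a rank test can give different answers for the same marker. With no precedence stated, a reader of the results could not tell which one was planned. The waiver of multiplicity adjustment applies across secondary outcomes. It does not settle which of two analyses of the same outcome counts.

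The Mann-Whitney test also suits this design poorly. It compares two groups on one number per patient, so it cannot use the samples at weeks 1, 7 and 13 jointly and cannot carry the planned covariates. The Limitations section itself expects heterogeneity across cancers and regimens. The same section wants the exploratory results to help identify endpoints and improve sample size estimates for later trials. That calls for an effect estimate with a variance, which a Mann-Whitney p-value does not provide.

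**Working it through.** **1. The plan's own figure.** The only sample size given is for the primary endpoint: difference 9.1, SD 13.7, two-sided alpha 0.05, power 90%.

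n per group = 2 × (1.960 + 1.282)² × 13.7² / 9.1² = 2 × 10.51 × 187.69 / 82.81 ≈ 47.6, so 48.

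This reproduces the stated 48. The exact t-test calculation gives 48.6, so 49, with 89.6% power at 48. This point does not touch that figure; 48 per arm is borrowed below because the article gives no number for the markers.

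**2. Do the two rules overlap?** Rule one covers laboratory data. Rule two covers immunological and metabolic parameters. The toxicity section lists metabolic and immunological biomarkers in its sentence on laboratory measures, and the Discussion calls glucose and cholesterol laboratory parameters. No sentence limits laboratory data to routine safety values. The rules therefore overlap as written.

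**3. Relative efficiency at one time point.** Assumptions: normal data and a baseline-to-follow-up correlation ρ of 0.3, 0.5 or 0.7.

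- Mann-Whitney against the t-test under normality: 3/π = 0.955.
- Variance of the baseline-adjusted contrast relative to the raw follow-up value: 1 − ρ² = 0.91 / 0.75 / 0.51.
- Variance of the change score relative to the raw follow-up value: 2(1 − ρ) = 1.4 / 1.0 / 0.6.
- Mann-Whitney on raw values against the adjusted model: 0.955 × (1 − ρ²) = 0.87 / 0.72 / 0.49.
- Mann-Whitney on change against the adjusted model: 0.955 × (1 − ρ²) / [2(1 − ρ)] = 0.955 × (1 + ρ)/2 = 0.62 / 0.72 / 0.81.

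**4. Simulation.** 4,000 trials per setting, 48 per arm, one follow-up time point, two-sided 5%. A linear model with baseline as covariate stands in for the mixed model.

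| | ρ = 0.3 | ρ = 0.5 | ρ = 0.7 |
|---|---|---|---|
| Power at 0.5 SD, Mann-Whitney on raw values | 64% | 65% | 65% |
| Power at 0.5 SD, Mann-Whitney on change | 50% | 66% | 86% |
| Power at 0.5 SD, baseline-adjusted model | 70% | 79% | 92% |
| No effect: at least one of model and raw Mann-Whitney has p<0.05 | 6.8% | 7.9% | 8.6% |
| 0.5 SD effect: model and raw Mann-Whitney disagree on significance | 12% | 19% | 29% |

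Each test alone stayed close to 5% with no effect. The last two rows pair the model with Mann-Whitney on raw values; the pairing with change scores was not computed.

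**5. Which markers have a pre-treatment value?** The immunological markers have one, at enrolment. Gamma-H2AX does not: under Table 1, footnote 1, and the Cell damage section it is first drawn on day 1 of cycle 1, after chemotherapy has been given.

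**The case against.** **The rules may not overlap.** The toxicity sentence can be parsed as laboratory measures and, separately, specific biomarkers. The section on body weight and safety uses laboratory assessments for blood counts and organ function. Table 1 gives immunological response its own line. On that view a general rule is followed by a specific one, and each marker has one method. This reading is possible, and it means that two p-values per marker are a risk, not something the text announces. But no sentence draws the boundary, and it does not fit metabolic markers such as glucose, which the Discussion calls a laboratory parameter.

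**Baseline may be used.** A reader might infer that the Mann-Whitney test ignores the enrolment sample. The documents do not establish this. Raw values are the more literal reading, because the BMI sentence names a change and this one does not. The Discussion, however, speaks of exploring changes. If changes are ranked, baseline is used.

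**The figures lean on assumptions.** This stands. The article gives no correlation. Normal data favour regression, and a rank test is a defensible choice for skewed markers. The number with immunological data is unknown, since the Ethics statement lets patients refuse the additional blood draws.

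**An article leaves detail to the full plan.** The marker list, scale and visit may be given there, and their absence is not criticised here. What remains is two rules in the published text that cover the same markers.

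**The outcomes are exploratory.** This also stands, and it limits the weight of the point.

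**Conclusion.** The point holds in a limited form. The published text assigns overlapping markers to two methods without precedence, and the second method fits repeated samples poorly. If both are run, with raw values ranked, the error rate per marker and time point is about 7% to 9% instead of 5%. The baseline-adjusted model has the higher power whether raw values or changes are ranked: 70% to 92%, against 64% to 65% or 50% to 86%. These ranges rest on ρ between 0.3 and 0.7, normal data, a 0.5 SD effect and 48 per arm. The gap could narrow for skewed markers or with fewer samples.

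It would go too far to say that the trial discards its baseline samples or will certainly report two p-values per marker. The text leaves both open. The primary endpoint and the sample size are unaffected.

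**What to change.** Name the mixed model already planned as the single main analysis for repeated laboratory, metabolic and immunological markers. Log-transform where values are skewed. Include the pre-treatment value as covariate where one is collected; this excludes gamma-H2AX, which has none.

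Delete the Mann-Whitney sentence for these markers, or keep it as a labelled sensitivity analysis that states the ranked variable and the time point.

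The cost is one or two sentences in the analysis section and no new data. The downside is a modelling assumption for skewed markers, which the transformation and the rank-based sensitivity check address.
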